We designed a randomized controlled trial with the primary aim of investigating the effect on mathematical achievement of incorporating physical activity in math teaching for 7-year-old schoolchildren. Secondary aims of the study were to investigate effects on executive function, and the longitudinal associations between PA and creativity, math, executive function, body mass index and aerobic fitness. The hypothesis was that PA integrated into classroom teaching would be superior to traditional, physically inactive classroom teaching in facilitating learning, and would be associated with a greater improvement in academic skills.

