## Methods

### Study design

The study was designed as a cluster-randomized controlled trial with two arms. In two municipalities in the southern part of Denmark, twelve elementary schools were randomized to either active math intervention (*n* = 7) or control (*n* = 5) (Fig. 1). Randomization was performed by random selection of sealed envelopes containing the intervention allocation stratified by municipality, in the presence of school leaders, municipality representatives and study researchers.

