### Recruitment of participants

We approached three municipalities in the Region of Southern Denmark with the aim of recruiting schools and 1st grade children to the study. One municipality (15 schools) declined to participate. We hypothesized that children in this age group would particularly benefit from a classroom-based PA intervention, as they were likely to be struggling to sit in the same position in lessons for the majority of the day. Schools in these municipalities were eligible if they did not have a structured program that incorporated PA in the classroom.

Out of the 48 eligible schools that were invited to participate in the study, 12 schools accepted (7 in Svendborg municipality and 5 in Kolding municipality). The 1st grade children in these schools were invited to participate in a letter describing the study, measurement methods, randomization procedure and consent form. The children, parents and teachers were then invited to a meeting at the school, where a full description of the scientific background and the study was given. After this, 90.7 % of parents gave consent for their child to participate in the study, corresponding to 505 out of 557 students in 26 different classes. The excluded children received the same intervention as their classmates but did not participate in testing. A flowchart illustrating the recruitment and randomization process is shown in Fig. 1.

In Svendborg municipality, the participating schools were all part of an existing intervention study that had been initiated in 2008 (the CHAMPS-study DK). This intervention consisted of four extra lessons of physical education (PE) each week, in addition to the two compulsory lessons, resulting in a total of 4.5 h extra per week, divided over at least three weekly sessions of at least 60 min (a more detailed description of the CHAMPS-study DK can be found in [48]). To ensure that the extra PE lessons in Svendborg municipality did not bias the results of the present study, randomization to the intervention was stratified by municipality.

All schools were co-educational schools, with gender integrated classes in all subjects, which is typical for the Danish educational system.

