### Teacher training for the intervention

Teachers in the intervention schools attended a 4-day mandatory course on how to integrate active math into the Danish curriculum for mathematics in public schools. The aim of the course was to provide the teachers with the skills to implement physically active math lessons, i.e. to use suggested methods and develop new ways of integrating physical activity into lessons, to organize the activities and to report on intensity of PA (for an overview of the course plan, see Appendix 2).

The research group developed the training course and the associated training material that included specific instructions and inspiration for how teachers could integrate PA as an element of academic instruction in math lessons. Examples from this material were used to help illustrate the practical dimensions of the active math lessons. It should be noted that the focus of the course was on developing the teacher’s own abilities to design active math lessons and thus their own pedagogical skills and knowledge rather than handing out a complete manual with activities for the math lessons. The course included an introduction to the study context and aims, with emphasis on creating high motivation among the teachers for the intervention by explaining the numerous potential positive cognitive effects of learning through action and describing previous findings related to PA in general. The teacher’s motivation for implementing PA in the classroom and their involvement are highly relevant matters for math achievement [61], and could influence the outcome of the study. The teachers thus played an active role in creating and developing the activities for the math lessons. Furthermore, several theories of how to develop activities in the classroom were presented e.g. the ‘Activity-wheel’ [62], with the purpose of creating activities that would help the children to reach the desired learning objectives.

On the last course day, active teaching techniques were discussed and related to motivational, organizational and management techniques. Several teachers attending the course highlighted the challenges they expected to face when implementing PA in math. This initiated an internet-based intra-school communication forum in each of the two municipalities, where the teachers shared activities, experiences and advice for the active math intervention. The teachers received normal salary for attending the course, as compensation for their time.

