### Classroom PA and total PA by students using accelerometry

The level of PA during math lessons and total daily PA were assessed using accelerometry (ActiGraph, GT3X and GT3X+, ActiGraph LLC, Pensacola, FL, USA). PA data were collected for eight days at baseline and again just before follow-up measurements. The accelerometers were randomly distributed by the research staff to all participants, who were instructed to wear the monitor during waking hours for at least eight consecutive days. Assessment periods were balanced between control and intervention schools. To eliminate reactivity bias, the monitors started recording the day after distribution. Epoch length was set to 2 s but subsequently downloaded in 10-s epochs. A sequence of more than 60 min of consecutive zeros was considered non-wear time and eliminated from the analysis. To account for children who failed to remove the monitor at night, only activity recorded between 6 am and 10 pm was analyzed. A valid measurement of total PA was defined as a minimum of four days with at least 10 h of recorded activity each day. For PA levels during math lessons only one valid day of measurement was required for inclusion in the analysis. Propero software (University of Southern Denmark, Odense, Denmark) was used to prepare the data for further analysis and to specify the time-points at which, according to the class schedule, math lessons took place. Total PA was expressed as mean counts per minute (cpm) and mean minutes in moderate-to-vigorous physical activity (MVPA) per day. Intensity cut-off points by Evenson et al. were used to define MVPA [73].

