### Statistics

Descriptive statistics according to outcome measures and relevant baseline characteristics will be calculated and compared across allocation groups.

Using conventional two-sided levels of significance (0.05) and statistical power (0.8) and given a sample size of 550 children from 12 different schools, the minimum detectable difference in the change in math score between the intervention and control group will be 0.9 points, assuming a standard deviation of the change in math score of 3.6 points. If a school-level cluster effect of 0.07 is taken into account, the minimum detectable difference in the change in math score will be 1.9 points.

The effect of the intervention will be tested using mixed effects regression models adjusted for relevant potential confounding factors that were not randomly distributed in children from the intervention and control schools (i.e. gender, age, baseline value of the variable, socioeconomic status). Because of the clustered nature of the data, schools will be included as random effects in the analyses. All data will be entered twice and thereafter checked manually for outliers. Analyses will be performed with statistical software STATA version 14.

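### School is the only random level named for the analyses; this suits the arm effect, but in associations between math-lesson physical activity and outcomes it leaves out class and understates the standard error

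*Protocol article*

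**What the plan says.** The protocol article, under Statistics, states that "The effect of the intervention will be tested using mixed effects regression models" with covariate adjustment. It adds that, because the data are clustered, "schools will be included as random effects in the analyses". This is the article's only rule on clustering in the models.

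Other sections describe the structure that the rule has to cover:

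- Study design: "twelve elementary schools were randomized to either active math intervention" or control, seven schools against five.
- Recruitment of participants: consent was given for "505 out of 557 students in 26 different classes".
- Background: the secondary aims include "the longitudinal associations between PA and creativity, math, executive function, body mass index and aerobic fitness".
- Teacher training for the intervention: "The teachers thus played an active role in creating and developing the activities for the math lessons". The course deliberately did not supply a complete manual of activities.
- Classroom PA and total PA by students using accelerometry: "The level of PA during math lessons and total daily PA were assessed using accelerometry", on each child.
- SMS-tracking and Appendix 3: teachers report active minutes for the class and their own motivation.

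**The concern.** PA in math lessons is partly a product of the teacher and class, so it can differ between classes in one school. Outcomes can also be correlated within class beyond school, since classmates share teaching and sit the math and creativity tests in a classroom. When exposure and outcome both vary between classes, a model with only a school intercept counts about 19 classmates as separate pieces of information on a difference that is largely between classes.

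At stake is the secondary aim on PA and outcomes. Intervals would be too narrow and p-values too small for the exposures closest to the trial's hypothesis, so links between classroom PA and achievement or cognition could be over-reported.

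**Working it through.** **1. The plan's own figures.** Inputs from Statistics: 550 children, 12 schools, SD of change 3.6, two-sided 0.05, power 0.80, school cluster effect 0.07 (read as an ICC).

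- Unadjusted, equal arms: (1.960 + 0.842) × 3.6 × √(1/275 + 1/275) = 0.86. With a 7:5 split it is 0.87. Both round to the stated 0.9.
- Design effect: 1 + (550/12 − 1) × 0.07 = 4.138.
- Adjusted, equal arms: 1.75 with normal quantiles and 1.94 with t quantiles on 10 degrees of freedom. The second matches the stated 1.9.

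The stated figures therefore reproduce with school as the unit. No class-level figure is given.

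**2. Formula for omitting class.** Mean class size is 505/26 = 19.42. Let ρ be the class ICC of the outcome beyond school, and s the share of PA variance between classes. Approximately:

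shortfall in SE = 1 − 1/√(1 + 18.42 × ρ × s)

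Examples:
- ρ = 0.05, s = 1: 1 − 1/√1.921 = 28%.
- ρ = 0.05, s = 0.3: 1 − 1/√1.276 = 11%.

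Both ρ and s are assumptions.

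**3. Simulation check.** School-only random-intercept model fitted by REML, 12 schools, 26 classes, 505 children, two class layouts, 1,500 runs per setting, assumed school ICC 0 to 0.07. Three kinds of PA measure were used:
- A: all variance at class or school level (s = 1 in the formula).
- B: half at class or school level (0.2 school, 0.3 class; s = 0.3).
- C: 15% at class or school level (0.05 school, 0.10 class; s = 0.1).

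| Class ICC | A: formula | A: simulated (type I error) | B: formula | B: simulated (type I error) | C: formula | C: simulated (type I error) |
|---|---|---|---|---|---|---|
| 0.02 | 15% | 13-16% (0.08-0.10) | 5% | 2-7% (0.06-0.07) | 2% | 1% (0.05-0.06) |
| 0.05 | 28% | 27-30% (0.15-0.16) | 11% | 10-13% (0.08-0.09) | 4% | 4-6% (0.06-0.07) |
| 0.07 | 34% | 31-36% (0.17-0.20) | 15% | 13-17% (0.09-0.11) | 6% | 3-7% (0.05-0.06) |
| 0.10 | 41% | 44-45% (0.26-0.27) | 20% | 18% (0.11) | 8% | 4-6% (0.06) |

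A separate simulation over the same ICC range gave 14-36% for A, about 5-19% for B and 2-8% for C. With class ICC set to zero, the shortfall was still −2% to 5%. Differences of a few percent are therefore not evidence of a class effect.

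**4. Arm effect.** In the same simulation, with school as the only random level, the SE shortfall was −2% to 7% with no trend by class ICC. Type I error was 0.03 to 0.06 with t on 9 degrees of freedom.

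**5. Does a class intercept repair the associations?** For a wholly class-level exposure, adding class and keeping maximum likelihood with normal-based tests left type I error at 8-11%. REML with t on 13 degrees of freedom brought it to 4-6%. Both the class intercept and the small-sample reference are needed.

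**The case against.** The sentence on random effects follows one about testing the intervention effect, and the article writes out no model for the associations. A condensed article may leave that model to a fuller plan, so its absence is no fault. This stands. However, the article does state a random structure for the analyses in general, and a reader applying it to the secondary aim would omit class.

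A reader might infer that the primary test is invalid too. The documents do not support that: schools were randomised, and step 4 shows no loss. Whether the arm test would be inflated under normal-based inference is a separate question, since the article states neither estimation method nor reference distribution.

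A reader might also infer that every PA association has a standard error 30-40% too small. By the formula, that needs a class ICC of about 0.056 to 0.096 and a PA measure that does not vary between classmates. Accelerometry is recorded on each child, even in math lessons, and total daily PA includes time outside school.

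Finally, teacher-reported minutes and motivation are described as measures of compliance. Nothing says they will be related to outcomes, or that each class has its own math teacher. The largest figures therefore apply only if such measures are used as exposures.

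**Conclusion.** The point holds in a limited form. The stated school-only structure is adequate for the randomised comparison and poorly suited to associations in which PA varies between classes. Assuming a class ICC of 0.02 to 0.10 beyond school, the standard error is understated as follows:

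- Math-lesson PA measured on the child, with half or less of its variance at class or school level: about 5-19%.
- A wholly class-level measure, such as teacher-reported dose or motivation, if used as an exposure: about 14-45%.
- Total daily PA, if it varies mainly between children: a few percent, which is hardly distinguishable from simulation error.

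The direction follows from the design that the article describes. The size rests on assumed values that the article does not give. This is a cheap improvement to a secondary analysis, not a defect in the primary one.

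**What to change.** Keep the school random intercept for the arm effect, with degrees of freedom based on the 12 schools. After the sentence on random effects, add:

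> In models relating math-lesson PA or any teacher-reported PA measure to outcomes, class nested within school will be included as an additional random intercept, with small-sample degrees of freedom.

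The cost is one sentence and one variance term. Class membership is already known, since math-lesson times were taken from the class schedule. The intervals for these associations become wider. With 26 classes in 12 schools, the class and school variances will be estimated imprecisely.

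The addition need not extend to the arm model. In simulation with REML and t on 10 degrees of freedom, type I error there was 4.2-5.0% with school only and 2.4-4.2% with class added, so the test gained nothing and became somewhat conservative.

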## Discussion

The literature lacks well-designed large-scaled randomized controlled trials on the effect of classroom-based physical activity on academic achievement and cognition. The present study will contribute to the field by generating detailed knowledge about the relationship between physical experiences that are combined with abstract math information and the acquisition of math skills. We expect the study results to provide schools and education policy-makers with an evidence base for implementing physical activity in daily school life, as a change from schoolchildren sitting still much of the day.

Apart from the large sample size and the comprehensive follow-up of children’s learning experiences and physical behavior over nine months, this study includes detailed measurement of the primary and secondary outcomes using well-validated methods. The math test applied in this study has been used for over 25 years to assess the math skills of Danish schoolchildren. The complex flanker task that assesses the three core executive functions will allow us to verify the few previous research findings concerning the association between a change in physical activity level and the ability to focus on a target stimulus and inhibit distractions [14, 74]. Furthermore, we expect the combination of SMS-tracking and accelerometry to be an excellent solution for measuring physical activity in large cohort studies. This makes it possible to compensate for some of the problems associated with accelerometry measurements, for example by using SMS-tracking to ask questions about specific activities, including water activities, and to allow more precise measurement of exercise intensity during cycling. When all this information is coupled to the class school timetable, then we can analyze the physical activity undertaken in specific time periods such as lunch breaks or during the math lessons. However, accelerometry does not provide any qualitative detail about the types or modes of activity being undertaken. For this reason accelerometry measurements were combined with video recordings of math lessons.

An important limitation of this study is the lack of qualitative data collection. This could have been used to further describe the various interventions and the complexity of the social contexts in which the active math was tested, (i.e. through case studies of a specific child/teacher or a specific context, observations of classroom activities, or qualitative interviews with children, teachers, and parents). Due to economic reasons, qualitative assessment was not performed since the main objective of the study was of quantitative character.

In conclusion, the results of this study will expand the current evidence on the relationship between physical activity and academic achievement in schoolchildren. We expect the results to stimulate the debate about whether the integration of physical activity into the classroom can enhance children’s cognitive skills and creativity, and will help educational practitioners to design learning environments that are optimal for cognitive development and academic achievement.

### Approval and registration

Ethics: Ethics committee of the Region of Southern Denmark (S-20140105)

Trial registration: clinicaltrials.gov (NCT02488460).

## Appendix 1

### Active math intervention - Example 1: Mathematics darts

#### Aim

The aim of this activity is to rehearse simple mental arithmetic, i.e. to become familiar with numbers, addition, subtraction and mixed operations.

#### Materials

Balls or small sandbags to throw. Plates (approximately 1 x 1 m) with painted numbers and arithmetic operators (+, −, x,/), or you could draw these on the blackboard or outside on the floor/ground. The plates are divided into different sections (plus, times, minus, divide, etc. and various numbers 0 to 9).

#### Process

Students paired two and two are equipped with the balls and throw them one at a time at the numbers and operators. The aim is to be the couple who “reach” a predetermined number, such as “300” as fast as possible with the fewest throws. If the first of a pair of students throws three balls and hits “4”, “9” and “time sign”, they can form the equation 4x9 = 36, and have earned 36 points. If the student only hits numbers and no operators, then it can be agreed that the numbers must be added, or that no points are achieved in that round. The second student then takes their turn, and they continue to alternate until someone reaches the agreed total score.

#### Variation and progression

This task is quite versatile and the students can work with elementary multiplication and simple division or they can work with more complicated math questions, decimals and fractions. They can also bring paper or chalk to write down the calculations and remember them.

- The operator signs can be varied (e.g. plus, minus, multiply, divide, power, square root, parentheses)
- The numbers on the plates can be varied (e.g. natural numbers, integers, fractions, decimals)
- The students can do the task individually, in pairs, or in groups with or without timed competition
- The number of balls thrown in each round can be varied.

### Active math intervention - Example 2: Skipping rope

In this activity, the children are divided into pairs and they skip calculations to each other. One child skips while the other counts. If the child skips on two legs, one skip counts for 10, and a one-legged skip counts for 1. Thus if a child jumps three times with both legs and two times with one leg, the answer will be 32. This activity can also be made with ‘minus’, by skipping backwards and ‘multiply’ by skipping once with arms crossed.

## Appendix 3

### Short message service (SMS)-tracking for teachers

- How many times have you started an activity where the students have gone from sitting still to being active (that is, where they get away from their chairs)?
- How many minutes has the class been active at low, moderate and high intensity?

One Friday every month, the teachers answered the following questions on motivation:

- How important do you think physical activity is to promote students’ acquisition of math on a scale of 1 to 6, where 6 is most important?
- How motivated were you this week to implement physical activity in math lessons on a scale of 1 to 6, where 6 is extremely high motivation?

### Short message service (SMS)-tracking for parents

1. “How many times did [NAME OF CHILD] engage in sports during the last week”?

The parents were instructed to answer with the relevant number between 0 and 8. The answers 0 to 7 reflected the unique number of times engaging in sports, while 8 stood for ‘more than 7 times’.

2) Which type of sports did [NAME OF CHILD] undertake?

The parents were instructed to answer with a number between 0 and 10. The answers 0 to 9 each represented a unique type of sport, while 10 stood for ‘something else’.

3) How many times has [NAME OF CHILD] cycled to school in the last week?

The returned answers were automatically recorded and inserted into a database. To improve compliance rates, the responders were contacted by telephone if the answer did not fit with the instructions. Furthermore, a reminder was automatically sent if a participant had not responded within 72 h and, if necessary, again within 120 h of receiving the message.

